#### **Risks and Discomforts (as communicated to the IRB)**

Subjects may feel uncomfortable being asked questions about their mood.

Subjects will be made aware that they are under no obligation to fill out the screening instruments and under no obligation to engage in PSE sessions, or to follow through with a referral to mental health care.

Subjects may feel uncomfortable engaging in PSE. Again, they will be made aware that participation is strictly voluntary and that if they do choose to participate, they are under no obligation to have their session audiotaped (which we ask permission for, in order to assess intervention fidelity).

Subjects may feel uncomfortable being referred to mental health care. They will be made aware that they are under no obligation to give us permission to see if they have accessed mental health care if referred.

It is unlikely that PSE will precipitate a mental health emergency, as this type of activity is mainly educational in nature and does not explicitly address depressive symptoms. Rather, it will be offered to mothers who display such symptoms or are at risk for depression. PSE allows for clients to discuss their daily practical life problems, such as getting their children to school on time, paying their bills, juggling multiple tasks, and leaves it up to the client to pick the problem that she will work through with the caseworker. However, in the event that a mental health emergency occurs, we will have a crisis management plan in place. The crisis management protocol is available in the study binder.

Potential risks for uncovering moderate to severe depression, substance use, domestic violence, or trauma symptomatology. All clients in both the PSE and non-PSE groups will be administered the MINI depression module, trauma symptom scale, DV questions, and substance use questions. In both study arms, part of the intervention will be to refer clients with moderate to severe depressive symptoms to mental health care.

We have developed a resource list to give to any subject that is interested in accessing further care. We also plan on using Boston-based BEST team for potential mental health emergencies. Although many measures will be taken to ensure confidentiality, there is the possible risk of a breach of confidentiality. If such a breach is determined to have happened, we will contact all subjects whom the breach affected immediately, explain to them exactly what happened and to our best approximation who had access to the data. We will also offer to work with the subjects in any way they deem appropriate to rectify the situation.

#### **Data Safety Monitoring Plan**

Throughout the course of the study, the data will be monitored every week by [name] in consultation with [name], statistician. Investigators will meet weekly with educators and research assistants to discuss cases and debrief on experiences. Monitoring will pay particular attention to adverse

events or events that had the potential to become adverse. In addition, as described above” we will continually monitor for events of suicidal ideation and activate a crisis management plan as necessary. In such an event, we will always notify the IRB and analyze if our plan functioned as expected.

[name], LICSW will be our data safety monitor. [name] is the director of BMC’s Child Witness to Violence Program and is an experienced therapist and mental health clinician. We will furnish [name] a de-identified dataset every 50 subjects with information on who required acute intervention and why in response to what study process/questionnaire item it was required. [name] will provide feedback to the study team regarding ongoing safety.

#### **Potential Benefits**

Based on previous evidence, it is likely that subjects' depressive symptoms will improve as a result of this intervention.

Women in a Major Depressive Episode or with high depressive symptoms will get referred to mental health care.

Women who are in a domestic violence situation, have substance abuse or dependence problems will also be referred to more definitive care through established medical and community-based organizations (see attached protocols)

Depression is a substantial public health problem, and preventing it among high risk mothers has substantial societal benefits in the areas of both health and education.

#### **Risk/Benefit Ratio**

We believe that the potential benefits of this project outweigh the risks. Previous data around access to care for young women with depressive symptoms consistently show that only a small minority of these women receive the necessary services. And since maternal depression is known to have ill effects for the child as well, leaving this condition untreated have repercussions for both the mother and child. If successful, this project will allow for a scalable and sustainable intervention for among a high risk population.

#### **Recruitment Procedures**

##### Recruitment Screen

Head Start caseworkers will obtain verbal consent from mothers to screen them for depressive symptomatology with the PHQ-2 and to assess recent depression history (Screening instrument is attached in study binder). This overlaps with current Head Start practice regarding screening mothers for depression.

##### Major Depressive Episode Screen

Mothers meeting either of these eligibility criteria will be offered to meet with a research assistant, who

will conduct a second verbal consent to screen for current MDE using the MINI MDE module.

Once the MINI is performed, research staff will obtain written consent, administer the in-person baseline survey, and randomly assign study allocation only if mothers meet the inclusion and exclusion criteria as outlined above (The baseline instrument is provided in the study binder).

Two important factors require us to temporarily record names of the potential subjects screened with this instrument:

- Screening for depression is part of normal Head Start practice through their "strength and needs assessment;" this initial screener will be done by Head Start staff. Therefore, Head Start sites have the option of using the PHQ2 AS BOTH A STUDY SCREENING INSTRUMENT AND A CLINICAL TOOL USED BY HEAD START STAFF. In order that it fulfill the latter purpose, an identifier is necessary - not for study personnel, but rather for Head Start personnel.
- Because Head Start staff will be conducting these initial screens (not study personnel), it is necessary that they be reviewed by study staff to most accurately determine ultimate study eligibility. We thus plan that study personnel review the screening results with Head Start staff.

We will therefore write the verbal consent form to explicitly inform potential subjects that this screening form will be reviewed one time by study personnel and that the information on the screen will not be recorded for any study purpose aside from what is mentioned above.

Furthermore, to safeguard confidentiality, the 'name' field will be replaced by a temporary study code. Head Start staff will keep the cross-walk between temporary codes and actual names in a separate location. The screening form, code, and cross-walk will all be destroyed as soon as study eligibility is determined.

A script for the initial case worker approach is will be kept in the study binder and provided to the IRB. We will also provide Head Start sites with study pamphlets to help introduce the research study in Head Start. These pamphlets will also be kept in the study binder and supplied to the IRB.

Recruitment Materials will all be available in the study binder.

#### **Data from Screening Procedures**

We will retain all data from screening procedures.

The initial screening data will be kept. We will include a de-identified data HIPPA waiver to collect pre-written informed consent aggregate data for ineligible mothers approached for the recruitment screen. In order to do this, we will attach a de-identified data form, which will be filled out by Head Start case managers. The following data will be collected: current gateway depression symptoms (depressed mood and anhedonia) and past depression history, depression symptoms based on DSM IV that may lead to a diagnosis of MDE.

Additionally, after written informed consent, we will retain data on ability to consent using Mac-CAT CR and level of suicidality based on MacArthur Suicide Screen.

#### **Consent Procedures**

RAs working for [name] will obtain consent and describe the informed consent process prior to definitively determining eligibility. Potential subjects will have as long as they wish to consider participating.

Our detailed consent and eligibility determination processes are as follows:

1. Head Start caseworkers will obtain verbal consent to screen clients for eligibility, as detailed above. We do this so mothers who are NOT at risk for depression-and therefore not appropriate for the study-will not be unnecessarily inconvenienced. This verbal consent and screen will occur in person or on the telephone. The latter mechanism is necessary because the mothers are frequently in phone contact with their Head Start caseworkers, but may not see them in person more than every month; and although the mothers will often come to Head Start to pick up their children, they usually do not see their caseworkers during this time (the verbal consent form is provided in the study binder). This process will be conducted by Head Start caseworkers.
2. Once caseworkers refer mothers who have screened positive for symptoms and/or a history, staff RA's will conduct a second verbal consent and screen additionally to see if the mother is currently in a Major Depressive Episode.
3. If mothers are eligible on recruitment screen AND are not currently in a Major Depressive Episode, written informed consent will be obtained by staff RAs. This will occur in person. The RA script for informed consent is provided in the study binder and will be supplied to the IRB. Research assistants will be trained to explain that written informed consent is required prior to eligibility screening due to the type of information collected. This is particularly important because if potential participants screen positive for suicidality, the study's crisis management protocol will be activated (available in binder and provided to the IRB).
4. Mothers will be explained during consent procedures that they will be randomized into either the supplement (H-31999) or the prevention trial (this protocol). If they are randomized into the prevention trial (this protocol), they will be explained that they will randomized a second time into the intervention or control group.
  - a. Because this protocol and the supplement to this protocol (H-31999) share the same consent form and we randomize only AFTER the consent form is signed, we will be using the consent form for THIS PROTOCOL (H-29448) for ALL participants, even those that will be later randomized to the supplement (H-31999). This is to maintain consistency between all consent procedures.
  - b. Any changes to the consent forms or procedures for this protocol or the supplement to this protocol (H- 31999) will be completed at the same time and no consent procedures will happen until both protocols are IRB aproved.
5. If we encounter an immature 15 or 16-year-old who would otherwise be potentially eligible, we will only take their informed consent if the person can actually give informed consent.
6. For all participants, we will use the MacArthur Competence Assessment Tool for Clinical research (MacCAT-CR) to determine participants' capacity to give informed consent. The MacCAT-CR instrument has been used widely in other clinical research studies and assesses a participant's

competence using four sections: understanding, appreciation, reasoning and expressing a choice. Please refer to study attachments for the customized MacCAT-CR.

For those who do not want to be screened and for those who ultimately opt not to participate, we will record only their temporary study ID, so that we do not inadvertently approach them again. We will submit this list of names to Head Start personnel, so they also know who has declined participation in the study and can give us de-identified demographic data as outlined in HIPPA section.

#### **Waiver of Documentation of Informed Consent**

Our waiver of documentation of informed consent applies only to the recruitment screening process and the Major Depressive Episode screening, and not any subsequent study procedures – for which written informed consent will be obtained.

#### **Payment**

All participants will receive a \$100.00 gift card to Target after completion of the three in-person research interviews: 1) Baseline, 2) 6-month interview and 3) 12-month interviews. Participants who cannot complete in person 6 and 12 month interviews will be given the option of doing the interviews over the phone and compensated with a \$50 gift card instead.

Participants will also receive \$25.00 gift cards for completion of 15 minute over-the-phone research interviews: months 2, 4, 8 and 10.

The gift cards for the phone research interviews will be disbursed to participants at their next in-person interview in order to facilitate distribution and to limit lost or stolen gift cards. Mothers who choose to have 6 or 12 month interviews over the phone rather than in-person, will be delivered gift cards via their Head Start case manager or via registered mail.

In addition to payments for time compensation, participants without their own form of secure telephone communication will be offered a cell phone with a monthly plan. This will be given only to participants who need the cell phone as defined in our cell phone incentive plan. The primary purpose of this cell phone incentive is to develop a system to ensure quality follow up data and to ensure participant safety.

#### **Attachments**

All individual safety protocols, scripts, data collection instruments, and pamphlets will be available in the study binder and supplied to the IRB

#### **Problem Solving Education Manual and Workbook**

The PSE manual and workbook is available in the study binder; workbooks are available in English and Spanish.

## Appendix – January 2018

The following appendix summarizes the content of an official letter written by the study PI to the National Institute of Mental Health in April 2010, specifying mediation and moderation analyses that were not included in the original grant application, in response to the NIH study section's summary statement (March 2010). This letter was requested by Program Official, [name]. The following summarizes the content of that letter. The letter itself is located in the study binder.

We outline an augmented analytic strategy to assess factors that have sound theoretical bases to either moderate or mediate the effect of PSE.

- a. *Theory based moderators:* Individual coping styles can substantially modify the effect of a problem solving intervention, as can the degree of baseline depressive symptoms. We proposed evaluate moderation by these factors by performing stratified analyses, followed by formal testing of interaction terms in our statistical models.
- b. *Theory based mediators:* According to our theoretical model (the Relational Problem Solving Model of Stress), improved problem solving skills and decreased perceptions of stress constitute likely intervention mediators; however, studies of other problem solving interventions have demonstrated impact in the absence of improved problem solving skills, problem resolution, or increased sense of mastery and self-control. Given PSE's emphasis on goal setting and action planning, a plausible alternative mechanism is behavioral activation, which we proposed to assess through the Behavioral Activation for Depression scale. We proposed to examine mediational effects using two potential techniques: the approach of Baron and Kenny and the use of path analysis models.

We detailed specific measures to reflect these constructs; each of these measures is listed in the main body of the trial protocol.

| Construct                               | Measure                                                                                                                                                                                                                                                                                     | Hypotheses                                                                                                                                                                                                                                                         |
|-----------------------------------------|---------------------------------------------------------------------------------------------------------------------------------------------------------------------------------------------------------------------------------------------------------------------------------------------|--------------------------------------------------------------------------------------------------------------------------------------------------------------------------------------------------------------------------------------------------------------------|
| Behavioral Activation                   | The Behavioral Activation for Depression Scale (BADs) addresses four dimensions: activation, avoidance/rumination, work/school impairment, and social impairment; this measure thus spans the affective and functional domains.                                                      | Behavioral activation will partially mediate the effect of the intervention, particularly with regard to functional outcomes.                                                                                                                                      |
| Mastery / Self-esteem                   | The Pearlin Mastery Scale , which measures the degree to which individuals perceive themselves as in control of their lives,  will be used in conjunction with the Rosenberg Self-esteem Scale .                                                      | Self-perceived mastery will correlate with depression symptoms and problem solving orientation. Mastery will be impacted by intervention exposure but will not mediate its effect.                                                                                 |
| Cognitive components of problem solving | The COPE characterizes an individual's coping styles (e.g. denial, disengagement, planning).
The Social Problem Solving Inventory -Revised (SPSI-R) measures problem orientation and problem-solving skills in 5 dimensions: positive and negative orientation; avoidance; | Baseline coping style will modify the effect of the intervention: those with avoidant styles will benefit to a lesser degree than those with planning or reframing styles.
Problem solving skills will correlate with depressed mood and will partially mediate |

|  |                                                                                                              |                       |
|--|--------------------------------------------------------------------------------------------------------------|-----------------------|
|  | impulsivity; and rationality and thus primarily addresses the cognitive component of problem solving skills. | intervention effects. |
|--|--------------------------------------------------------------------------------------------------------------|-----------------------|

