### Sample Size Justification

Based on empiric longitudinal data that we have collected among a cohort of Head Start mothers, we describe the size of detectable interventional effects with adequate statistical power for each primary outcome. All estimates assume 80% power and a two-sided alpha of 0.05.

- i. Problem solving skills. The mean problem solving (SPSI-R) score among mothers in our observational study is 12.2, (SD 2.5); women with  $\geq$  moderate depression symptoms have a mean score of 14.7 (SD 2.2) and those with  $\leq$  mild symptoms have a mean score of 9.8 (SD 2.8;  $p > 0.0001$ ). Using a two-sample t-test, a sample size of 100 per group will be able to detect a very granular one-point difference in mean SPSI-R scores between study groups (a standardized effect size of 0.4).

- ii. Incident rate of moderate to severe symptomatic episodes. Using poisson regression analysis, with 100 subjects in each study group and a poisson rate of 1.2 spikes per 5 follow-up assessments in the control group (according to our current data), we can detect a reduction in the rate of spikes to 0.8 in the treatment group – a 33% reduction in symptomatic episodes.
- iii. Depressive symptoms over time. In our longitudinal data, we have observed the following mean QIDS scores for each follow-up month and assume these values for the control group in the planned study: 8.2; 7.6; 7.5; 6.9; 7.2 (common SD, 5.9). We hypothesize that the following mean QIDS scores in the treatment group would be achievable and clinically significant: 7.2; 6.6; 5.5; 4.4; 4.2, resulting in a mean difference of 3 points in QIDS scores across study groups (note: a 3-point difference in QIDS scores, in the majority of cases, would move a subject across a clinical cutoff corresponding to mild, moderate or severe symptoms). Using a two group repeated measures design analyzed by generalized estimating equations or mixed linear models, noting within-subject correlations of 0.7 for values separated in time by one month and 0.6 for those separated for two months or more in our longitudinal analysis), we can detect the above differences in the means between groups over time with 100 subjects per study group.

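### The appendix names the Baron and Kenny steps beside path analysis without saying which decides mediation; the steps are gated on the total effect and detect mediation less often than a direct test of the indirect effect

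*Protocol*

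**What the plan says.** Part b (theory-based mediators) of the protocol's January 2018 appendix reads: "We proposed to examine mediational effects using two potential techniques: the approach of Baron and Kenny". The sentence then adds path analysis models. The two stand side by side, with no order and no rule for the case in which they disagree. The steps themselves are not written out.

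The table of constructs in the same appendix states what is expected. For behavioral activation: "Behavioral activation will partially mediate the effect of the intervention, particularly with regard to functional outcomes". For problem solving: "Problem solving skills will correlate with depressed mood and will partially mediate" the intervention effects. Mastery is expected to respond to PSE but not to mediate.

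The trial was sized for total effects only. The Sample Size Justification says "All estimates assume 80% power and a two-sided alpha of 0.05", and for problem solving that "a sample size of 100 per group will be able to detect a very granular one-point difference in mean SPSI-R scores between study groups", described as "a standardized effect size of 0.4". It gives no effect size or power for mediation.

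**The concern.** The causal-steps approach, as commonly applied, asks for separate significant results: arm on outcome (c), arm on mediator (a), and mediator on outcome given arm (b), with a direct effect (c′) smaller than c. The product a·b, which is the indirect effect, is never estimated or tested. Two consequences follow.

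- **Gate.** A trial with clear a and b paths is still declared negative for mediation if c misses 5%. At about 80% power for c, that happens often.
- **Label.** A common convention calls mediation full when c′ is not significant and partial when it is. Because c′ is smaller than c by construction, true partial mediation is easily reported as full.

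Both named techniques use the same data and can disagree, and the appendix does not say which answer stands. At stake is the mechanistic conclusion about PSE. The predicted absence of mediation by mastery is also affected, because a procedure that misses real mediation more often confirms such a null too easily.

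**Working it through.** **1. The plan's own figure.** SPSI-R: "mean problem solving (SPSI-R) score among mothers in our observational study is 12.2, (SD 2.5"), difference 1 point, so 1/2.5 = 0.4 SD. With 100 per arm, z = 0.4 × √(100/2) = 2.83, and power = Φ(2.83 − 1.96) ≈ 0.81. The stated 80% is reproduced. This 0.4 is used as path a.

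**2. Total effect on QIDS.** The treatment means are "7.2; 6.6; 5.5; 4.4; 4.2, resulting in a mean difference of 3 points in QIDS scores across study groups". Against the listed control means (8.2, 7.6, 7.5, 6.9, 7.2) the differences are 1, 1, 2, 2.5 and 3. Their average is 1.9, and 3 is reached only at the last visit. With SD 5.9 and correlation 0.6, the mean of six follow-up scores has SD 5.9 × √((1 + 5 × 0.6)/6) = 4.82, so c = 1.9/4.82 = 0.394 SD. Using the five listed visits, with 0.6 throughout or 0.7 for adjacent ones, gives 0.39 or 0.38. The 3-point difference gives 3/5.9 = 0.51 SD.

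Power for c: 0.394 × √50 = 2.79 gives about 80%; 0.51 SD gives about 95%.

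**3. Assumed.** The share mediated, p, is not in the protocol; 30% to 70% is used. Then b = p·c/a and c′ = (1 − p)·c. Within-arm SDs are set to 1.

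**4. Power for the direct effect.** The squared correlation of arm and mediator is (0.4²/4)/(1 + 0.4²/4) = 0.0385. Hence SE(c′) = √(1 − b²) × √(1/(200 × 0.25 × 0.9615)) = √(1 − b²) × 0.144. At p = 50%: b = 0.49, SE = 0.126, c′ = 0.197, z = 1.57, power about 35%. At 30% and 70% the same formula gives about 52% and 20%.

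**5. Simulation at c = 0.394, a = 0.4, 100 per arm, 10,000 trials per row.** The joint test (a and b both significant) stands in for a test of the indirect effect.

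| Share mediated | Steps find any mediation | of which called partial | of which called full | Joint test |
|---|---|---|---|---|
| 30% | 64.5% | 38.4% | 26.1% | 79–81% |
| 50% | 69.0% | 27.5% | 41.5% | 79–81% |
| 70% | 71.1% | 15.9% | 55.2% | 79–81% |

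The middle columns are percentages of all trials. Repeat runs agree within about 2 points. A percentile bootstrap of the indirect effect at 50% mediated (300 trials) gave 83%. Every trial passed by the steps also passes the joint test, so the two techniques disagree in about 9 to 15 of 100 trials (80 − 71 to 80 − 65).

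**6. Sensitivity to the total effect, a = 0.4.**

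- At 0.51 SD, with one third, one half and two thirds mediated, the steps find 77.6%, 78.7% and 80.2%, against 80.5%, 80.2% and 80.6% for the joint test. The gap is 3 points or less. The full label is given in 19.4%, 29.4% and 32.4% of trials, and in about 17% when 30% is mediated.
- At 0.24 SD, fully mediated (illustrative, outside the protocol's hypotheses), the steps find 37% against 80%.

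With a = 0.5 the detection gap is wider: 70.5% against 90.2% at c = 0.384 with one third mediated, and 89.5% against 93.8% at 0.51 SD.

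**7. Does an interval establish partial mediation more often?** The check was whether the bootstrap interval for the proportion mediated lies wholly inside 0–100% (800 trials, 600 resamples). At 30%, 50% and 70% mediated it did so in 41%, 30% and 17% of trials, against 40%, 29% and 16% called partial by the steps. A repeat run gave 42%, 28% and 15% against 40%, 28% and 16%. There is no gain. The median interval width was 0.8 to 1.1.

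**The case against.** Several points on the other side are sound.

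- The appendix already names path analysis, which can supply the indirect effect. A reader might infer that the plan relies on the causal steps alone. It does not. The defect is that two unequal methods are listed with neither deciding.
- A reader might also infer that mediation needs a significant direct effect, so that the plan would show its hypothesis in only 16% to 39% of trials. The documents do not support that. The appendix states no such rule, and significance of c′ is a labelling convention, not a condition for mediation. The figure is the chance of the label partial under assumed inputs. An interval for the proportion mediated does no better (step 7), so low power for that question comes from the sample size and is not peculiar to the steps.
- The mediated share and path b are assumed. The average QIDS difference includes months 2 and 4, before SPSI-R is first measured at 6 months. No effect size is given for functional outcomes, so the figures say nothing about behavioral activation.
- The details might be left to a statistical analysis plan, and the appendix only summarises a 2010 letter. This limits the weight of the point but does not remove it: the protocol itself puts the weaker method on an equal footing.

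**Conclusion.** The point holds as a limited one about method choice. On a total QIDS effect of about 0.39 SD, a mediator effect of 0.4 SD, 100 per arm and an assumed 30% to 70% mediated, the steps lose roughly 9 to 15 percentage points of detection against a test of the indirect effect. The loss is near zero at 0.51 SD and larger for smaller total effects. If full mediation is read from a non-significant direct effect, 26% to 55% of trials with true partial mediation are mislabelled at 0.39 SD, and about 17% to 32% at 0.51 SD with the same mediator effect.

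The power to establish partial mediation is about 15% to 42% at 0.39 SD under either method. The partial-mediation hypotheses are therefore best treated as matters of estimation. Only supplementary mechanism conclusions are affected; the primary analyses of problem solving, symptomatic episodes and QIDS over time are untouched.

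**What to change.** Keep the appendix as the record of what was proposed, and add to it or to the statistical analysis plan:

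- The indirect effect from the path model, with a bootstrap 95% CI, is the deciding mediation analysis.
- It is reported together with the direct effect and its CI, whatever the p-value of the total effect.
- Full or partial mediation is not inferred from the p-value of the direct effect. The partial-mediation hypotheses are reported as estimates with intervals, with a note that the trial has little power to separate partial from full.
- Any Baron and Kenny results are descriptive only.

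The cost is a few sentences. The data are the same, path analysis is already named, and bootstrap intervals take negligible extra work.
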